## Abstract

**Background:**

Although CT colonography is a less invasive alternative for colonoscopy for the detection of colorectal polyps and cancer, procedural pain is common. In several studies, CT colonography pain and burden is higher than in colonoscopy. Apart from discomfort, anxiety and its related stress-induced peri- procedural side effects, this may influence the adherence for CT colonography as a possible screening tool for colorectal cancer. We hypothesize that a single bolus intravenous alfentanil will give a clinically relevant reduction in maximum pain defined as at least 1.3 point reduction on an 11-point numeric rating scale (NRS).

**Methods/Design:**

A randomized double-blind placebo-controlled trial in which patients scheduled for elective CT colonography in a single tertiary centre are eligible for inclusion. The first 90 consenting patient will be block-randomized to either the alfentanil group or the placebo group. Before bowel insufflation, the alfentanil group receives a single bolus intravenous alfentanil 7.5 μg/kg dissolved in 0.9% NaCl, while the placebo group receives an intravenous bolus injection of pure 0.9% NaCl. For both groups an equal amount of fluid per kilogram (75 μL/kg) is injected. The primary outcome is the difference in maximum pain on an 11-point NRS. Secondary outcomes include: pain and burden of different CT colonography aspects, side effects, procedural time and recovery time. For the primary outcome an independent samples t-test is performed and a P value < 0.05 is considered statistically significant.

**Discussion:**

This study will provide evidence whether a single bolus intravenous alfentanil gives a clinically relevant reduction in maximum pain during CT colonography.

**Trial registration:**

Netherlands Trial Register (NTR): NTR2902

*This trial will be conducted in accordance with the protocol and in compliance with the moral, ethical, and scientific principles governing clinical research as set out in the Declaration of Helsinki (1989) and Good Clinical Practice (GCP). The department of radiology of the Academic Medical Center of Amsterdam is responsible for the design and conduct of the trial*.

## Background

Computed tomographic (CT) colonography is an equally accurate and less invasive alternative for colonoscopy for diagnosing colorectal cancers and large- to medium-sized polyps [1-3]. The method is used in clinical practice while it has been adopted as colorectal cancer screening tool in the USA and is being considered as such in other countries [4,5]. Although CT colonography is less invasive than colonoscopy, pain is frequently observed during bowel insufflation [6-12]. Insufflation is a prerequisite for accurate visualization of the bowel wall [13]. Bowel insufflation causes stretching of the bowel and may result in colonic cramp which causes pain. In some studies pain and/or burden of CT colonography even compares unfavourably with conventional colonoscopy under conscious sedation [6-8].

Apart from the discomfort, anxiety and its related stress-induced side effects peri- procedural the, the experienced pain may well reduce the adherence of CT colonography as a potential screening tool for colorectal cancer. Especially in a screening setting - where the majority of participants does not benefit from the scan - participants will give a substantial weight to pain and burden compared with symptomatic patients who are much more likely to benefit from the scan.

During conventional colonoscopy administration of analgesics is standard. To the best of our knowledge, no analgesic is administered during CT colonography. To induce sufficient analgesia during CT colonography an opioid will be necessary. Studies using preventive oral analgesic agents for acute pain often do not result in a significant pain reduction [14-17]. In colonoscopy opioids are routinely used, often in combination with a benzodiazepine because of the synergetic effect [18,19]. CT colonography is expected to be less painful compared with colonoscopy without the administration of analgesic medication. A benzodiazepine as co-medication is therefore probably not required. Because of a procedural time of about 20 minutes a short acting opioid like fentanyl or alfentanil will be sufficient and thus prevents long recovery times [20-22]. An opioid bolus has been shown to improve pain scores during sigmoidoscopy [23]. Alfentanil has the advantage of being one of the most short-acting opioids and with the shortest recovery time [20-22]. The need for recovery facilities could have detrimental consequences on the clinical use as well as for CT colonography as a screening tool and this favours alfentanil [24].

Alfentanil is a relatively safe drug, but has possible side effects like other opioids such as: nausea, vomiting, hypotension, bradycardia and respiratory depression. However, in low- to medium-dose and without the use of a benzodiazepine, the incidence respiratory depression is extremely low [20,22,25,26]. In a study of Cho et al. a bolus injection of 10 μg/kg alfentanil did not induce any hypoxemia, desaturations or apnoeas [26].

Before considering analgesia in CT colonography, clinically relevant pain reduction, burden and acceptance, without detrimental effects on safety and cost-effectiveness should be demonstrated. For assessment of pain during a procedure, a numeric rating scale (NRS) is often used instead of a visual analogue scale (VAS), because it can be assessed verbally. We have experience with an 11-point NRS for pain assessment during our CT colonography procedure and therefore these data can serve as pilot data. A reduction of 1.3 points on an 11-point NRS is considered the minimum clinically relevant pain reduction [27-29]. To evaluate the effect of an intervention with medication such as alfentanil in CT colonography, a randomized (placebo) controlled trials is the optimal study design. As alfentanil is dissolved in a 0.9% saline solution, an ideal placebo would be 0.9% saline, above all because the colour and viscosity is similar.

We therefore perform a randomized double-blind placebo-controlled trial to evaluate the effect of a single bolus intravenous alfentanil of 7.5 μg/kg on the pain during CT colonography. We hypothesize that a single bolus intravenous alfentanil will give a clinically relevant reduction in maximum pain defined as at least 1.3 point reduction on an 11-point NRS. To the best of our knowledge no previous study evaluated the use of analgesia in CT colonography.

## Methods/Design

### Objectives

#### Primary objective

To evaluate whether a single intravenous alfentanil bolus (7.5 μg/kg) has a clinically relevant analgesic effect in patients undergoing elective CT colonography compared with placebo. We have defined a clinically relevant effect as a pain reduction of 1.3 point on an 11-point NRS [27,29].

#### Secondary objectives

To assess the difference in:

• Pain score in all insufflation positions (right and left decubitus, supine and prone) and the average pain score

• Pain and burden of all CT colonography aspects (bowel preparation with oral iodinated contrast and diet, cannula insertion, rectal catheter insertion, insufflation, positional change on table and period after the procedure), and total pain and burden of CT colonography

• Side effects of alfentanil during CT colonography including:

○ respiratory effects (apnoea, respiratory frequency, and blood oxygenation)

○ hemodynamics (heart rate and blood pressure)

• Procedure and recovery time

• The most painful and most burdensome aspect of CT colonography

### Trial design

This study will be a single-centre randomized double-blind placebo-controlled trial.

### Population

Consecutive 90 patients between 18 and 85 years from the Academic Medical Center (AMC) of the University of Amsterdam, who give informed consent, will be included. The population in the AMC scheduled for CT colonography is a mixed group of sexes, ethnic backgrounds, and mostly elderly patients.

### Exclusion criteria

• Hypotension (systolic blood pressure < 90 mmHg)

• Bradycardia (heart rate < 50 beats per minute)

• Severe chronic obstructive pulmonary disease

• Known allergy for alfentanil

• Pregnancy (if the patient indicates any chance of being pregnant, this will be tested)

• Known severe liver disease defined as a Child-Pugh score of > 4

• Use of MAO-inhibitors or within two weeks before the CT colonography procedure

• Use of barbiturates, opiates or daily benzodiazepine use

• Known increased intracranial pressure

The number of excluded patients and the reasons for their exclusion will be recorded and also reported in the following article.

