### Sample size

The sample size calculation was aimed at the detection of a difference in pain score between the alfentanil and placebo group. We calculated average pain score and standard deviation of a population screening trial performed in the AMC where the same insufflation procedure and 11-point NRS were used. The standard deviation was 2.6 in the pilot data. Based on our clinical experience with alfentanil we assume alfentanil will cause a reduction of 1.5 on an 11-point NRS. We tested this with a one-sided test, using 0.05 significance and 80% power. An independent samples t-test to compare means in two groups in nQuery Advisor 7.0, results in groups of 38 subjects. With an anticipated withdrawal rate of approximately 5%, we aim to include 45 patients per group.

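### Minor safety point: only daily benzodiazepine users are excluded, so a patient who took an occasional dose shortly before the scan may still receive the alfentanil bolus

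*Protocol article*

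**What the plan says.** The relevant line under Exclusion criteria reads "Use of barbiturates, opiates or daily benzodiazepine use". The qualifier *daily* attaches to benzodiazepines only. The same list gives another drug class a time window: "Use of MAO-inhibitors or within two weeks before the CT colonography procedure".

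The Background touches on benzodiazepines three times:
- On colonoscopy practice: "In colonoscopy opioids are routinely used, often in combination with a benzodiazepine because of the synergetic effect".
- On this trial: "A benzodiazepine as co-medication is therefore probably not required".
- On alfentanil's safety: "in low- to medium-dose and without the use of a benzodiazepine, the incidence respiratory depression is extremely low".

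The Informed consent section has the exclusion criteria checked in the recruitment telephone call, and patients may decide to take part until two days before the scan. The Safety section names respiratory depression as the most serious adverse event of alfentanil in this setting. No section bars a recent, non-daily benzodiazepine dose.

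**The concern.** For an acute interaction, what counts is whether the drug is present when the bolus is given. Daily use is a poor stand-in for that. A patient who rarely takes a sedative but took one the evening before meets the printed criteria, while the protocol's own reassurance is worded for the case without a benzodiazepine. The Abstract and Background both mention anxiety around the procedure, so an occasional tablet beforehand is plausible, though the document gives no frequency.

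At stake is avoidable exposure of a few participants to a combination that the protocol itself calls synergetic. The integrity of the comparison between the arms is not at stake.

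**Working it through.** **1. The text, side by side.**

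| Drug class | Excluded when | Recency window |
|---|---|---|
| Barbiturates | any use | none stated |
| Opiates | any use | none stated |
| MAO-inhibitors | current or recent use | two weeks |
| Benzodiazepines | daily use only | none stated |

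A single dose the night before is not daily use, so the patient passes.

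**2. Does a later check close the gap?** The telephone call cannot capture a tablet taken after it. Some criteria, such as "Hypotension (systolic blood pressure < 90 mmHg", imply a measurement closer to the scan. But a later check that applies the printed wording would still admit this patient.

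**3. The plan's own figure.** The Sample size section uses an SD of 2.6, a difference of 1.5, a one-sided 0.05 level and 80% power, and "results in groups of 38 subjects". This reproduces. With noncentrality 1.5 / (2.6 × √(2/38)) = 2.51 and 74 degrees of freedom, the noncentral t distribution gives power 0.801 at 38 per group, against 0.792 at 37. Adding a recency window changes none of these inputs, so 38 evaluable and 45 enrolled per group stand.

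**4. Scale of exposure.** The document gives no rate of recent occasional use. The values of p below are assumptions chosen to show a range. The arm size of 45 and the total of 90 come from the Sample size and Population sections.

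| Quantity | Formula | p = 1% | p = 3% | p = 10% |
|---|---|---|---|---|
| Expected exposed on alfentanil | 45p | 0.45 | 1.35 | 4.5 |
| At least one exposed on alfentanil | 1 − (1 − p)^45 | 36% | 75% | 99% |
| Ineligible per 90 arrivals | 90p | 0.9 | 2.7 | 9 |
| Extra arrivals to randomize 90 | 90p / (1 − p) | 0.9 | 2.8 | 10 |

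The first two rows describe the plan as written and count exposure, not respiratory events. The second treats patients as independent. The last two are the cost of the fix if the question is asked before randomization.

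**The case against.** The strongest reply is that the Background passage is about sedation given with the procedure. It describes colonoscopy practice and then explains why this trial needs no benzodiazepine as co-medication. Read that way, the safety clause means no co-administered sedative, and the trial gives none. Whether the studies cited there excluded patients who had taken a tablet at home cannot be known from this document. The word *daily* may also be a deliberate clinical choice.

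The safeguards are extensive:
- pulse oximetry throughout;
- infusion over about two minutes;
- an operator trained in advanced life support;
- oxygen, bag-mask ventilation and naloxone at hand;
- a rescue plan, with the on-call anaesthesiologists informed of every examination;
- an hour of observation;
- exclusion of severe chronic obstructive pulmonary disease.

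The dose of 7.5 μg/kg is below the 10 μg/kg bolus for which the Background reports no hypoxemia, desaturation or apnoea. The study also has ethics approval. Finally, this is a condensed article, and day-of-scan medication questions may well stand in the full protocol or in site instructions.

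Most of this stands and limits how serious the point is. It does not remove it. The criterion is a printed rule that admits the patient, so the gap is more than missing detail. Since the trial gives no benzodiazepine, the patient's own intake is the remaining route to the combination. Monitoring and rescue detect and treat an event, but they do not prevent the exposure.

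A reader might infer that the protocol contradicts itself. It does not: the Background clause is mainly about co-medication, and an exclusion limited to daily use is compatible with it. A reader might also infer a raised rate of respiratory depression, or bias or lost power. The document offers no basis for an event rate, nothing here favours one arm in the analysis, and no sample-size input is affected.

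**Conclusion.** The point holds as an optional suggestion. The printed criterion lets a patient with a recent occasional benzodiazepine dose receive alfentanil, and the protocol's own remarks on synergy and on its most serious adverse event are reason enough to prefer a tighter rule. Expected exposure runs from under one to between four and five of the 45 alfentanil patients. That range rests entirely on the assumed 1% to 10% rates. The clinical risk per exposed patient cannot be judged from the document. The conclusion also rests on taking the printed exclusion list as the operative one.

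**What to change.** Reword the benzodiazepine criterion along these lines: daily benzodiazepine use, or any benzodiazepine intake within a window before the procedure set by the anaesthesiologists. Twenty-four hours, longer for long-acting agents, is only an example; the document supplies no basis for a particular length. The MAO-inhibitor line shows that the list already accommodates a window.

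Confirm it with one recorded question on arrival (any benzodiazepine, which one, when), asked before randomization and before the research physician prepares the syringe. The order matters. Asked first, a positive answer gives a pre-randomization exclusion, who is replaced and reported under the existing commitment: "The number of excluded patients and the reasons for their exclusion will be recorded". Asked after allocation, it would leave a randomized patient without the study drug, a complication the plan does not now have.

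The cost is one edited line, one question, and allocation and syringe preparation that wait for the answer. A few patients would be found ineligible on the day, with about 1 to 10 extra arrivals needed to randomize 90 under the assumed rates. Occasional users would be slightly less represented. The sample size does not change.

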### Sample size

The sample size calculation was aimed at the detection of a difference in pain score between the alfentanil and placebo group. We calculated average pain score and standard deviation of a population screening trial performed in the AMC where the same insufflation procedure and 11-point NRS were used. The standard deviation was 2.6 in the pilot data. Based on our clinical experience with alfentanil we assume alfentanil will cause a reduction of 1.5 on an 11-point NRS. We tested this with a one-sided test, using 0.05 significance and 80% power. An independent samples t-test to compare means in two groups in nQuery Advisor 7.0, results in groups of 38 subjects. With an anticipated withdrawal rate of approximately 5%, we aim to include 45 patients per group.

### Informed consent

Patients scheduled for an elective CT colonography procedure will be asked by telephone to participate [Figure 1]. The exclusion criteria will be checked during this conversation and if they are eligible for inclusion and interested in participating in our study, the patient information will be sent. Patients are included after written informed consent. Patients may decide to participate in our study until two days before CT colonography.

**Figure 1 F1:**
[figure not shown]
**Flow chart according to the CONSORT statement 2010**.

### Intervention

Subjects randomized to group 1 will receive alfentanil (Rapifen, Janssen-Cilag, Tilburg, the Netherlands) 7.5 μg/kg intravenously through a 20 Gauge intravenous cannula. Subjects randomized to group 2 will receive a placebo, in this study a 0.9% saline solution 75 μL/kg through a 20 Gauge intravenous cannula. For both groups an equal amount of fluid (75 μL/kg) will be injected. This placebo is chosen because alfentanil is dissolved in 0.9% saline solution. After administration of the spasmolytic agent the line is flushed with 5 mL 0.9% and again after administration of the study medication. Both the physician performing the CT colonography scans as well as the patient are blinded to the allocated group. Oxygen saturation, heart rate, and blood pressure will be measured during the CT colonography procedure, using a pulse oximeter and automated blood pressure monitor. A pain evaluation will be performed during insufflation in left decubitus, right decubitus, supine and prone position (see section pain evaluation).

Two questionnaires with 22 and 17 questions, mostly multiple-choice, will be given during this study: the first before randomization and the second after completion of CT colonography.

### CT colonography

Both preparation and insufflation are performed as used in current clinical practice in our institution. The preparation for CT colonography consists of two bottles of 50 mL iodinated contrast, meglumine ioxithalamate (Telebrix, Guerbet, Aulnay sous Bois, France), the day before and one bottle in the morning of CT colonography and a low-fibre diet for these days [30]. Colonic distension will be obtained by the automated administration of carbon dioxide (PROTOCO2L, Bracco, EZEM, Lake Success, USA) through a flexible 20 French rectal tube after intravenous administration of 1 mL (20 mg) butylscopalamine bromide (Buscopan, Boehringer-Ingelheim, Ingelheim, Germany) or, if contraindicated 1 mL (1 mg), Glucagon (GlucaGen, Novo Nordisk A'S, Bagsvaerd, Denmark). Insufflation takes place in three positions: right decubitus, left decubitus, and supine position. The aim is to insufflate three litres of carbon dioxide with 1.3, 0.9, and 0.8 litres per position, respectively. After five minutes the insufflation is stopped, whether the target of three litres is reached or not. The scan is performed using a 64-slice CT scanner (Brilliance, Philips Medical Systems, Best, the Netherlands) using dose modulation. A scan is performed in both supine and prone position. In case of clinical suspicion of colorectal cancer, 100 mL intravenous iodinated contrast agent, iopromide (Ultravist 300, Bayer B.V., Mijdrecht, the Netherlands) will be administered in supine position. Otherwise both series are unenhanced.

Parameter unenhanced CT: 120 kV

40 reference mAs

64 × 0.625 collimation

0.9 mm slice thickness

Parameters contrast-enhanced CT: 120 kV

200 or 250 reference mAs

64 × 0.625 collimation

0.9 mm slice thickness

### Analgesia

One of the two independent research physicians, who are in control of the randomization list, will prepare the alfentanil or the placebo. Subsequently, a blinded qualified physician, who performs the CT colonography, will infuse the medication/placebo via the intravenous cannula over a period of approximately two minutes. The medication/placebo is given 1.5 minutes after butyl scopolamine or glucagon is given and the average blood pressure and heart rate has been recorded. Butyl scopolamine influences the heart rate and blood pressure. After 1.5 minutes the effect of butyl scopolamine on the heart rate and blood pressure is present and a reliable baseline value can be registered.

### Monitoring

During the whole procedure, the patients will be monitored using a pulse oximeter. An automatic blood pressure device will monitor the blood pressure before administration of the spasmolytic agent and 1.5 minutes after the spasmolytic agent is given intravenously. After the first blood pressure measurement the blood pressure is automatically measured and recorded every five minutes. The heart rate and oxygen saturation is continuously recorded by pulse oximetry.

### Pain evaluation

During the procedure pain is assessed immediately after insufflation in left decubitus, right decubitus, supine and after scanning in prone position using an 11-point NRS. This score starts at 0, meaning no pain at all and ends at 10 means the worst pain imaginable. The score therefore contains 11 points. All four pain scores will be reported.

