### Statistical analysis

SPSS version 16.0 is used for all statistical calculations. A P value of 0.05 is defined as significant. Baseline characteristics are summarized with descriptive statistics. For categorical data the numbers or proportions are given, for normal distributed data the mean and standard deviation and for not normal distributed data the median with percentiles.

Differences between the alfentanil group and the placebo group will be tested for significance. For the calculation of differences in pain scores per position, average, and the maximum pain score during the procedure will be calculated using an independent samples t-test.

Differences in burden of different aspects of the procedure as well as the total procedural burden will be calculated using a chi-square test. Differences in the most burdensome aspect will also be calculated using the chi-square test. Differences in procedural time and recovery time will be calculated using an independent samples t-test.

We will test the associations between the baseline characteristics (independent variables mentioned below) and pain scores. As we consider the pain scores as continuous data, for this approach we will perform linear regression analyses.

Univariate analyses will be performed with pain scores as dependent variable and the following variables as independent variables: age, sex, BMI, education, ethnicity, expected burden, scan indication (including abdominal pain), known diseases and diagnosis, and whether it is the first CT colonography. Subsequently, the variables with a P value < 0.1 will be included in the multivariate analysis. In case more than four variables turn out to result in a P < 0.1, the four most influential variables will be used in the multivariate analysis. A stepwise backward selection strategy will be used, with a P value < 0.05 considered statistically significant.

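### No pain score is taken before the study drug although patients with abdominal pain can enter, so pain on arrival cannot be adjusted for; the cost is precision, not validity

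*Protocol article*

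**What the plan says.** **Outcome and analysis.** The Abstract (Methods/Design) states: "The primary outcome is the difference in maximum pain on an 11-point NRS". The Statistical analysis section compares the maximum score between groups with an unadjusted independent samples t-test.

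**Who can enter.** Informed consent: "Patients scheduled for an elective CT colonography procedure will be asked by telephone to participate". The Exclusion criteria contain nothing on current or abdominal pain. The nearest item is "Use of barbiturates, opiates or daily benzodiazepine use", which removes only some patients with ongoing pain. The Statistical analysis section lists, as possible predictors of the pain scores, "scan indication (including abdominal pain), known diseases and diagnosis, and whether it is the first CT colonography", so patients referred for abdominal pain are expected in the sample.

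**When pain is scored.** The drug comes first: "Before bowel insufflation, the alfentanil group receives a single bolus intravenous alfentanil". Pain evaluation then fixes the schedule: "During the procedure pain is assessed immediately after insufflation in left decubitus, right decubitus, supine and after scanning in prone position". It speaks of four scores in all. The scale's anchors refer to pain in general, not to pain from the procedure.

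**What is recorded before the drug.** The Analgesia section provides a pause of 1.5 minutes after the spasmolytic so that, for heart rate and blood pressure, "a reliable baseline value can be registered". The pre-procedural questionnaire, as summarised under Questionnaires, covers demographics and expected pain and burden. Current pain is not listed.

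**The concern.** The maximum of the four scores contains whatever pain the patient brought to the scanner as well as the pain of insufflation. Patients will differ in the first component. If arrival pain predicts the maximum score, that difference is noise in the primary comparison, and a measured baseline could remove it. With about 45 patients per group, the groups may also differ in arrival pain by chance, and nobody could tell.

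This goes beyond what an analysis plan could settle. Such a plan can add a covariate but cannot supply a measurement that was never taken, and the scoring schedule is set in the protocol itself. The regression planned under Statistical analysis does not fill the gap: it looks for predictors of pain, its list of independent variables does not include treatment, and scan indication is a reason for referral rather than pain intensity on the day.

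**Working it through.** **Inputs from the Sample size section.** SD 2.6; assumed difference 1.5; one-sided 0.05; power 80%; 45 per group; withdrawal about 5%.

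**1. The plan's own figure.** n = 2 × (1.645 + 0.842)² × 2.6² / 1.5² = 37.15, which rounds up to 38. The exact t-based calculation gives 37.85, again 38. The stated 38 per group is reproduced, and this point does not touch it.

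**2. Evaluable patients.** 45 × 0.95 = 42.75, taken as 43 per group.

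**3. Precision as planned.** SE = 2.6 × √(2/43) = 0.561. With t(84) = 1.989, the 95% half-width is 1.989 × 0.5607 = 1.115, or 1.12 points.

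**4. Precision with a baseline score as covariate.** Residual SD = 2.6 × √(1 − r²), where r is the correlation between the pre-drug score and the maximum score. The document gives no r, so a range is shown. The degree of freedom spent on the covariate is ignored; it does not change the rounded half-widths.

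| Assumed r | Residual SD | Variance removed (r²) | SE | 95% half-width | Power, one-sided | Power, two-sided |
|---|---|---|---|---|---|---|
| 0 | 2.60 | 0% | 0.56 | 1.12 | 0.843 | 0.753 |
| 0.2 | 2.55 | 4% | 0.55 | 1.09 | 0.856 | 0.770 |
| 0.3 | 2.48 | 9% | 0.53 | 1.06 | 0.872 | 0.792 |
| 0.5 | 2.25 | 25% | 0.49 | 0.97 | 0.922 | 0.863 |

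Power is for a difference of 1.5 with 43 per group.

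**5. Chance imbalance.** For an assumed SD of arrival pain of 1 or 2 points, the SE of the between-group difference in mean arrival pain is 1 × √(2/43) = 0.22 or 2 × √(2/43) = 0.43. The 95% ranges are about ±0.42 and ±0.85. This does not pass one-for-one into the outcome. The regression slope is r × 2.6 / (baseline SD), so the shift in the estimated effect has a 95% range of ±1.96 × r × 0.561: ±0.22 at r = 0.2, ±0.33 at r = 0.3, ±0.55 at r = 0.5. The threshold for clinical relevance is 1.3. These shifts are already part of the SE of 0.56 and must not be added to it.

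**6. Bias and dilution.** An illustrative simulation used 43 per group and 4,000 replicates. Arrival pain was assumed to have mean 3 and SD 1.5, to be unaffected by the drug, and to set a floor under the maximum. With 0%, 20% and 40% of patients in pain on arrival, the two-sided type I error was 4.7%, 5.2% and 4.8%. Simulation error is about √(0.05 × 0.95 / 4000) = 0.3 percentage points, so all three agree with 5%. The mean observed difference, for a shift of 1.5 in procedural pain, was 1.43, 1.35 and 1.27. The drop from 1.5 to 1.43 comes from the limits of the scale; the further drop is dilution by arrival pain.

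**The case against.** The opposing case is strong on four counts.

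*Validity.* A reader might infer that the primary comparison is biased. It is not. Allocation is random and blinded, so arrival pain is balanced in expectation, and a t-test on a post-treatment score is a standard, valid analysis. This stands in full.

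*The outcome.* A reader might also infer that maximum pain is the wrong outcome because it is not confined to pain caused by the procedure. The document does not support that. Its target is maximum pain during the examination, and total pain is a reasonable target given the Background's concern with burden and adherence. On that target, the dilution in step 6 is simply part of the true effect. Nor would a covariate isolate procedural pain or undo the floor; it improves precision and corrects chance imbalance.

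*Correctability.* It would go too far to say that nothing can be done about existing pain. Scan indication, including abdominal pain, is recorded and would allow a crude adjustment or a subgroup look. What cannot be recovered is intensity on the day.

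*Size.* Neither r nor the share of patients in pain on arrival is in the document. Abdominal pain as a reason for an elective referral need not be present on the table, and opiate users are excluded. The SD of 2.6 comes from a population screening trial, so applying r to it for clinical patients is an approximation. The gain could be nil.

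Two lesser objections carry less weight. The 22 and 17 questions of the two questionnaires are not shown in full, so an item on current pain cannot be ruled out. But the first questionnaire is sent with the consent form, so it is unlikely to capture pain just before the drug, and the numeric score is fixed at four time points. The haemodynamic baseline has its own reason, the effect of the spasmolytic. It therefore does not show that a pain baseline was overlooked, only that there is a moment to take one.

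**Conclusion.** The point holds as a cheap improvement, not as an error. Patients with abdominal pain can enter, every pain score follows study drug and insufflation, and no pre-drug score is described, so arrival pain intensity cannot be adjusted for. Scan indication is a crude proxy, and no treatment comparison adjusted for it is described.

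The test keeps its type I error. The cost is a residual variance larger than it need be by an amount that depends wholly on r: 0% could be removed at r = 0 and 25% at r = 0.5, with the SE going from 0.56 to between 0.56 and 0.49. Chance imbalance would go unseen. Dilution arises only if the effect of interest is on procedural pain and if arrival pain is common and untouched by the drug, which are assumptions. The claims that the trial is biased, that its outcome is unsuitable, or that existing pain is beyond any correction are not supported.

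**What to change.** In Pain evaluation, add one spoken 0 to 10 score, taken in the existing 1.5-minute pause when baseline heart rate and blood pressure are recorded and before the study drug is injected. In Statistical analysis, keep maximum pain as the primary outcome and compare the groups by analysis of covariance with this score as the one prespecified covariate. Eligibility and treatment stay as they are.

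The cost is a question of a few seconds, one covariate and a small amendment. Patients already enrolled would lack the value, so the amendment should say how they enter the adjusted analysis. If r proves to be near 0, practically nothing is gained and practically nothing is lost.
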